### Secondary Outcomes

For sub Trial I, secondary outcomes will be the following: Neurological impairment will be evaluated using the NIHSS (Time Frame: baseline, and on days 14, 28, and 42 during treatment). Self-rating symptoms will be evaluated using a visual analog scale (VAS) (Bijur et al., 2001). This will include VAS scores for limb numbness, swelling of hands or feet, and spontaneous sweating (hemilateral sweating) (Time Frame: baseline, and on days 14, 28, and 42 during treatment, as well as at day 14 after treatment). Continuous changes in the Modified Rankin Scale score (Uyttenboogaart et al., 2005) (Time Frame: baseline, at day 42 during treatment, and at day 90 after onset) will also be recorded. Activities of daily living will be measured using the Barthel Index (BI) score (Uyttenboogaart et al., 2005) (Time Frame: baseline, at day 42 during treatment, and at day 90 after onset).

For sub Trial II, secondary outcomes will include the following: Changes in the Seattle Angina Questionnaire (SAQ) score (Time Frame: baseline, at day 28 during treatment, at day 14 after treatment, and at day 90 after recruitment). Self-rating symptoms will be evaluated using a VAS for chest tightness, chest pain, palpitation, fatigue, and spontaneous sweating (Time Frame: baseline, and on days 14, 28, and 42 during treatment, as well as at day 14 after treatment).

In sub Trial III, the secondary outcomes will be as follows: Changes in the Toronto Clinical Scoring System (Bril and Perkins, 2002) (Time Frame: baseline, and on days 14, 28, and 42 during treatment, day 14 after treatment, as well as day 90 after recruitment). Self-rating symptoms will be evaluated using a VAS for local pain, limb numbness, and paresthesia (e.g., burning sensation, formication, electrical sensation) (Time Frame: baseline, and on days 14, 28, and 42 during treatment, as well as at day 14 after treatment).

For all sub trials, quality of life will be measured as a secondary outcome, using the 36-Item Short Form Survey (SF-36) (Time Frame: Baseline, at day 42 during treatment, and at day 90 after onset/recruitment). Blood, urine, and feces samples will be collected at baseline and day 42 for metabolomics, proteomics, microbiota, and flow-cytometry studies.

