### Statistical Methods

Statistical analysis will be performed using Statistical Analysis System version 9.4 (SAS Institute Inc., Cary, North Carolina, United States) statistical software packages. Outcome measurements will be analyzed using full analysis sets and per protocol sets according to intention-to-treat (ITT) analysis. Safety analysis will be performed in a safety set, which is defined as a subset of subjects who received at least one treatment and had actual safety indicators record data. The statistical analysis will include baseline characteristics of participants, compliance and concomitant medication, efficacy analysis and safety analysis. For continuous data, we will describe the results using the mean (standard deviation, SD), maximum, minimum, median and non-parametric test median (quartile deviation, QD). Categorical data will be described as absolute values and proportions. For continuous outcomes, paired *t*-test or Wilcoxon signed-rank test will be used to analyze significant differences between baseline and each time point. The Wilcoxon rank-sum test will be employed for comparisons between treatment groups. Chi-squared test will be used for categorical data and Wilcoxon rank-sum test will be used for ranked data. Analysis of covariance (ANCOVA) will be used to control potential confounding variables.

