We will use a two-sided 5% significance level and 85% power. Baseline characteristics in each group will be analyzed using descriptive statistics. Compliance analysis will be based on full analysis sets, and analysis of concomitant medications will be based on safety sets. Regarding the primary outcome variable, between-group comparisons of the change in syndrome score will be analyzed between pre- and post-treatment using paired t-test or Wilcoxon signed-rank test. As to the secondary outcomes, comparisons of the changes in NIHSS score in sub Trial I, the Seattle Angina Questionnaire score in sub Trial II, and the Toronto Clinical Scoring System in sub Trial III, will be analyzed using paired t-test or Wilcoxon signed-rank test between baseline and each time point. The Wilcoxon rank-sum test will be employed for comparisons between treatment groups. Any factors impacting efficacy, such as age and sex, should be taken into account as covariate. Safety will be analyzed in terms of all the adverse events occurred during the trial, and the incidence will be compared between groups using the chi-squared test or Fisher’s exact probability method.

Last observation carry forward (LOCF) approach will be used to impute missing data of primary outcome according to intention-to-treat analysis. A sensitivity analysis will be conducted to determine the robustness of the results under the missing at random assumption, to evaluate the role of lost to follow-up (i.e., participants who did not follow-up to V4), by using the LOCF method. And a *p* value of less than 0.05 will be considered statistically significant.

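### For NIHSS, SAQ and TCSS the plan fixes neither the deciding between-arm analysis nor the deciding visit, and does not name the baseline score as a covariate

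*Protocol article*

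**What the plan says.** The protocol article's Statistical Methods section states several things about the main disease scales, NIHSS (sub Trial I), SAQ (sub Trial II) and TCSS (sub Trial III):

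- The quantity of interest is change: "comparisons of the changes in NIHSS score in sub Trial I", and likewise for the other two scales.
- These changes "will be analyzed using paired t-test or Wilcoxon signed-rank test between baseline and each time point".
- Between arms: "The Wilcoxon rank-sum test will be employed for comparisons between treatment groups".
- On covariates: "Analysis of covariance (ANCOVA) will be used to control potential confounding variables", and later "Any factors impacting efficacy, such as age and sex, should be taken into account as covariate".
- On the threshold: a p "value of less than 0.05 will be considered statistically significant".

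The Secondary Outcomes section gives each scale several post-baseline visits. For TCSS the schedule is "Time Frame: baseline, and on days 14, 28, and 42 during treatment, day 14 after treatment, as well as day 90 after recruitment". No visit is singled out for any of the three scales.

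**The concern.** There are three linked weaknesses in what is stated.

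First, a paired test against baseline within an arm says whether patients changed, not whether the drug changed them. Natural recovery, regression to the mean and placebo response can all make it significant.

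Second, the between-arm analysis is ambiguous. The named test cannot take covariates, while nearby sentences call for covariates and ANCOVA. The text does not say which one decides. The strongest available covariate is likely to be the baseline value of the same scale. It is measured but not named.

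Third, no visit decides. Day 42 cannot be read as an unspoken default for all three scales, because the Secondary Outcomes text lists no day-42 SAQ assessment.

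The trial is meant to supply preliminary efficacy evidence in three diseases and to inform a phase III trial. That calls for a precise between-arm estimate at a visit chosen beforehand. With visit and method both open, the most favourable p-value can be presented as the result.

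**Working it through.** **Inputs from the protocol article.** Post-baseline visits (Secondary Outcomes): NIHSS 3 (days 14, 28, 42); SAQ 3 (day 28, 14 days after treatment, day 90); TCSS 5 (days 14, 28, 42, 14 days after treatment, day 90). Threshold 0.05. Patients: 432 / (3 diseases × 2 arms) = 72 per arm per disease before dropout.

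**Figure to reproduce.** There is none. The article gives no error rate for secondary outcomes. The statement "We will use a two-sided 5% significance level and 85% power" comes with no effect size or SD. All correlations and effect sizes below are therefore assumptions.

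**Step 1: within-arm tests.** Assume a mean change of 0.4 SD of the change score in an arm of 72. The test statistic is centred at 0.4 × √72 = 3.39, so the chance of p<0.05 is about Φ(3.39 − 1.96) = Φ(1.43) ≈ 92%. This holds for placebo as much as for BQTL. Sub Trial I recruits 14–30 days after stroke onset, when recovery without any drug effect is plausible.

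**Step 2: between-arm tests, if run at every scheduled visit.** Count: 3 + 3 + 5 = 11. With independent tests and no effect:

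- NIHSS: 1 − 0.95³ = 14.3%
- SAQ: 1 − 0.95³ = 14.3%
- TCSS: 1 − 0.95⁵ = 22.6%
- Any of the 11: 1 − 0.95¹¹ = 43.1%

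Visits of one scale are correlated, so I also use a simulation (200,000 runs, sub trials independent, equal correlation between visits):

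| Assumed correlation between visits | Chance of at least one false positive in 11 |
|---|---|
| 0.5 | 37.7% |
| 0.6 | 35.2% |
| 0.7 | 32.5% |
| 0.8 | 29.0% |

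With one named visit per scale, the chance is 5% within each sub trial and 1 − 0.95³ = 14.3% over the three.

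**Step 3: precision.** Let σ² be the variance of the score, equal at baseline and follow-up, and r their correlation. The variance of a change score is 2σ²(1 − r). The residual variance after adjusting for baseline is σ²(1 − r²). The ratio is (1 − r²) / [2(1 − r)] = (1 + r)/2. The power columns assume 72 per arm and a true difference of 0.4σ.

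| r (assumed) | Variance ratio | Power, mean change | Power, baseline-adjusted |
|---|---|---|---|
| 0.3 | 0.65 | 53% | 71% |
| 0.5 | 0.75 | 67% | 79% |
| 0.7 | 0.85 | 87% | 92% |
| 0.8 | 0.90 | 97% | 98% |

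The comparator here is a comparison of mean changes. The planned test is a rank-sum test, for which the gain would be similar but not identical.

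**The case against.** The strongest reply is that these are secondary outcomes in a phase II trial, reported in a condensed article. A hierarchy of secondaries, a full covariate list and a repeated-measures model are commonly left to the full protocol or SAP. That stands as far as omissions go, and I do not fault the article for lacking a multiplicity scheme. It does not answer the choices that are stated: within-arm tests at each visit, and a covariate-free between-arm test next to a call for covariates. The Discussion also says that the article presents a detailed analysis plan.

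Several stronger readings are tempting, and the document does not support them:

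- *Chance findings are near certain.* Counting every scale, VAS item and visit gives 21 + 25 + 19 = 65 tests and 1 − 0.95⁶⁵ = 96.4%. That requires pooling three separate patient populations and treating all tests as independent. Under the correlations assumed in different simulations it is roughly 65–92%. The scales in the quoted sentence give only 11 tests.
- *The rank-sum test runs at every visit.* This is an inference. The wording about each time point attaches to the paired tests, which is why Step 2 is conditional.
- *There is no baseline adjustment.* This is too absolute. Changes are compared, ANCOVA is planned in general terms, and age and sex are given only as examples.
- *These scales are the only check on disease benefit.* They are not. The modified Rankin Scale, the Barthel Index and symptom VAS items are also listed.
- *The primary result is compromised.* Testing secondaries without adjustment does not raise the primary outcome's error rate.

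**Conclusion.** The point holds in a limited form and should be acted on. For NIHSS, SAQ and TCSS, the plan gives prominence to tests that do not compare treatments. It names a between-arm test that cannot use the baseline score, and it leaves open which analysis and which visit decide.

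If all 11 scheduled visits are tested between arms, the chance of at least one false positive is about 43% if the tests are independent and 29–38% at assumed correlations of 0.8 to 0.5. The precision forgone by not adjusting for baseline depends on r. It is substantial at r = 0.5 (variance ratio 0.75) and small at r = 0.8 (0.90, with power moving only from 97% to 98% in the example). These ratios assume equal variances at baseline and follow-up and use mean change as the comparator. The article gives no data from which r could be estimated.

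**What to change.** For each of the three scales:

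1. Make the between-arm analysis a baseline-adjusted ANCOVA, or one longitudinal model with arm, visit, arm-by-visit, baseline score and baseline-by-visit. State that this analysis decides.
2. Name one visit as the key secondary contrast: day 42 for NIHSS and TCSS. SAQ has no day-42 assessment in the Secondary Outcomes text, so choose one of its scheduled visits and fix it before unblinding. Its day-28 visit falls before the end of the 6-week treatment and the other two fall after it, so the choice should be explained.
3. Report the other visits and the VAS items as between-arm estimates with 95% confidence intervals and no claim of significance.
4. Keep within-arm changes from baseline as description only.

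The cost is a change of wording and a modest amount of programming on data already being collected, with no new patients or visits. The downside is that fewer results can be called significant.

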## Abstract

**Background:** BuqiTongluo (BQTL) granules are herbal phenotypic drugs for Qi deficiency and blood stasis (QDBS) syndrome. Its discovery relied primarily on knowledge of observable phenotypic changes associated with diseases. Although BQTL granules have been widely advocated by Chinese Medicine (CM) practitioners, its use lacks empirical support.

**Aim of the study:** In this basket trial, the efficacy of BQTL granules in multiple diseases that have the QDBS syndrome in common will be compared with placebo.

**Materials and Methods:** The BuqiTongluo granule for Qi deficiency and blood stasis syndrome (BOSS) study is a basket herbal trial (ClinicalTrials.gov, NCT04408261). It will be a double-blinded, randomized, placebo-controlled, parallel, multicenter, clinical trial. In total, 432 patients (1:1:1 ischemic stroke, stable angina pectoris, and diabetic peripheral neuropathy), who meet the operationalized diagnostic criteria for QDBS syndrome, have been recruited and randomized in a ratio of 1:1 to receive 6 weeks’ treatment with BQTL granules or placebo. The primary outcome is the change in the QDBS syndrome score at week 6 from baseline. Secondary outcomes include objective outcome measures for the three diseases and adverse events. Omics will help to understand these responses by molecular events.

**Conclusion:** QDBS syndrome is a common phenotypic marker that was hypothesized to predict whether patients with multiple diseases would respond to this targeted therapy. No previous basket trial has assessed the potential efficacy of an herbal intervention for multiple diseases. The unique promise of the trial is its ability to exploit a disease phenotype to discover novel treatments for three diseases for which the root cause is unknown, complex, or multifactorial, and for which scientific understanding is insufficient to provide valid molecular targets.

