## Materials and Methods

### Study Design

The BuqiTongluo granule for Qi deficiency and blood stasis syndrome (BOSS) study is a basket herbal trial studying the effect of BQTL granules across multiple cohorts of three diseases (ClinicalTrials.gov, NCT04408261). The BOSS protocol includes three multicenter randomized, double-blinded, placebo-controlled sub trials that will study BQTL granules in three independent patient populations: ischemic stroke (sub trial I), stable angina pectoris (sub trial II), and diabetic peripheral neuropathy (sub trial III). This study is currently open at 14 sites across China. In each sub trial, patients will be randomly divided into an intervention group (BQTL granule) and placebo group (placebo) using an 1:1 allocation ratio, adhering to the Standard Protocol Items: Recommendations for Interventional Trials (SPIRIT) statement (Chan et al., 2013). The study period includes 6 weeks of medication and 90 days of follow-up. The study procedure is summarized in the CONSORT diagram (Figure 1), and the schedule of enrolment, interventions, and assessments is summarized in Table1. The trial will be performed in accordance with the Declaration of Helsinki and Good Clinical Practice Guidelines. Informed consent will be obtained from all participants.

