### Sample Size

For a main phase II trial assessing natural drugs, according to the NMPA recommendation (No. 28, 2007 and No. 109, 2018) and data from our pilot study, the sample size should not be less than 60 per treatment arm for each disease to estimate the parameter. We enrolled 432 participants to allow for dropouts.

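### The decisive between-group analysis of the QDBS change score is not settled, and the ANCOVA has an open covariate rule that does not name the baseline score

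*Protocol article*

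**What the plan says.** The Abstract defines the endpoint: "The primary outcome is the change in the QDBS syndrome score at week 6 from baseline". The Study Design section sets 1:1 randomisation within each of three disease sub trials, described as independent populations.

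The Statistical Methods section then gives four statements that bear on the comparison of arms:

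- As a general rule, and again straight after the secondary outcomes: "The Wilcoxon rank-sum test will be employed for comparisons between treatment groups".
- For the primary outcome, the between-group comparison of change in syndrome score is assigned to a paired t-test or a Wilcoxon signed-rank test.
- An ANCOVA is planned to deal with possible confounders.
- The covariates are governed by one sentence: "Any factors impacting efficacy, such as age and sex, should be taken into account as covariate".

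The section does not rank these methods. It does not name the baseline QDBS score as a covariate. It states no analysis that pools the sub trials.

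**The concern.** Three things go wrong together.

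First, the tests named for the primary between-group comparison do not compare groups. A paired t-test or signed-rank test asks whether one arm changed from its own baseline. The general rule points to a different test, and the ANCOVA is a third possibility. Whoever reports the trial could defend any of them as the planned analysis.

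Second, the covariate rule makes a relation to efficacy the entry criterion. Such a relation can be judged from the trial's own outcome data, and nothing says the choice must be made before unblinding. In a randomised comparison, covariates are there to gain precision and should be listed beforehand.

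Third, the obvious covariate for a change score, the baseline value of the same scale, is not mentioned. The rank-sum test cannot take it and gives no mean difference. Yet the Introduction makes optimising parameters for a phase III trial part of the first aim, and the Sample Size section sizes the trial to estimate a parameter.

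**Working it through.** **Inputs from the article.** Level and power: "We will use a two-sided 5% significance level and 85% power". Minimum size: "the sample size should not be less than 60 per treatment arm for each disease to estimate the parameter". Total 432, hence 432/6 = 72 per arm per disease. No dropout rate is given; 60/(1−d) = 72 implies d = 16.7%. With no effect size or SD stated, neither the 60 nor the 85% power can be reproduced.

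**Assumed, because not stated.** The correlation r between baseline and week-6 QDBS score; the ratio k of baseline SD to week-6 SD; normal data.

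**Variance.** Take the week-6 SD as 1.

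- Change score: 1 + k² − 2rk
- ANCOVA on baseline: 1 − r²
- Ratio: (1 − r²)/(1 + k² − 2rk), which is (1+r)/2 when k = 1

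| r | ratio, k = 1 | saving | ratio, k = 0.7 | saving |
|---|---|---|---|---|
| 0.3 | 0.65 | 35% | 0.91/1.07 = 0.85 | 15% |
| 0.5 | 0.75 | 25% | 0.75/0.79 = 0.95 | 5% |
| 0.7 | 0.85 | 15% | 0.51/0.51 = 1.00 | 0% |

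The ratio never exceeds 1. It equals 1 when k = r, because the regression slope r/k is then 1 and the change score is already the best adjustment.

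**Power at 60 per arm.** Choose the effect that gives an unadjusted t-test on change exactly 85% power: (1.960 + 1.036) × √(2/60) = 0.547 SD of change. For the same effect:

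- Rank-sum test, efficiency 0.955 under normality: 83.4%.
- ANCOVA, k = 1: 96.1% (r = 0.3), 93.3% (r = 0.5), 90.1% (r = 0.7), 88.5% (r = 0.8).
- ANCOVA, k = 0.7, r = 0.5: 86.8%.
- Patients per arm needed by ANCOVA for 85% power, k = 1: 60 × (1+r)/2 = 39, 45, 51 and 54 at r = 0.3, 0.5, 0.7 and 0.8.

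**Sub-trial term, only if the sub trials are pooled (180 per arm).** Power moves from 85% to 85.7%, 86.7% or 88.5% if disease explains 2%, 5% or 10% of the variance.

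**Open covariate choice.** Simulation under no treatment effect, 60 per arm, 2,000 runs, keeping the smallest p-value over all covariate subsets, where R² is the share of outcome variance the covariates explain:

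| covariates | R² | type I error |
|---|---|---|
| 2 | 0.1 | 7.9% |
| 4 | 0.1 | 8.6% |
| 4 | 0.3 | 13.1% |
| 6 | 0.3 | 15.5% |

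The nominal level is 5%. This is a worst case: it supposes unblinded selection of the most favourable model.

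**The case against.** The plan is not confined to an unadjusted rank-sum test. It includes an ANCOVA, and its covariate sentence offers age and sex only as examples. Baseline QDBS score is therefore unnamed, not excluded. Factors that affect efficacy can also mean known prognostic factors, no selection procedure is described, and statisticians stay blinded until the trial is completed. A full covariate list is commonly left to a statistical analysis plan, which is not shown here. Group means and SDs are to be reported, so a crude difference will be available whatever test is used.

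Most of this stands and limits the point. It does not remove it. The complaint concerns a rule that is written down, not a missing detail: an analysis plan that followed it would inherit both the open criterion and the conflict over the primary test. The Discussion also says that the article presents a detailed analysis plan. Blinding protects the error rate only if the covariates are fixed while it holds, and no sentence ties the two together. Crude means and SDs are not an adjusted difference with its interval and residual SD.

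A reader might also infer that a pooled test ignores the disease strata. The article states no pooled test. Within one sub trial there is no disease stratum to adjust for, so that argument is conditional on pooling.

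**Conclusion.** The point holds in this form: three unranked methods for comparing arms, one of them not a between-group test, and an ANCOVA with an open covariate rule that does not name the baseline score. This should be corrected, and the conclusion does not depend on the power figures.

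The size is uncertain. With equal SDs at both visits, the variance saving over an unadjusted change score is 15% to 35% for r from 0.7 to 0.3. At 60 per arm, ANCOVA gains about 3.5 to 11 points of power over a t-test on change (r from 0.8 to 0.3), and about 5 to 13 points over the rank-sum test. It would be wrong to read these as a floor. All patients must have the syndrome at entry, so a narrower spread at baseline is plausible, and with k = 0.7 the saving at r = 0.5 falls to about 5%.

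The 8% to 15% type I error shows what the wording could allow. It is not a prediction. Two stronger readings, that baseline is excluded or that only an unadjusted analysis is planned, are not supported by the text.

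**What to change.** Before unblinding, in the protocol or analysis plan:

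1. Name one primary analysis: ANCOVA of the week-6 QDBS score on treatment and baseline QDBS score, with a closed covariate list of age and sex. Add sub trial only if the sub trials are pooled.
2. Report the adjusted mean difference, its 95% CI and the residual SD.
3. Use the same form for NIHSS, SAQ and TCSS, each with its own baseline.
4. Keep the rank-sum test as a sensitivity analysis, stratified by sub trial if data are pooled.
5. Delete the sentence admitting any factor that affects efficacy, and confine the paired and signed-rank tests to within-arm description.

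Centre terms are optional: 14 sites across a sub trial of about 144 patients average about ten each, so the terms would be sparse and use up degrees of freedom.

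The cost is wording. Baseline scores, age, sex and sub trial need no new data collection.

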### Primary Outcomes

The primary outcome of the study is improvement in QDBS syndrome, defined as a change in the national approved QDBS syndrome evaluation scale from before to after the 6-week treatment. The QDBS syndrome evaluation scale (Wang et al., 2015) was chosen because of its practical use in the evaluation of the QDBS syndrome. The scale is a 21-item clinician-rated scale with anchored item descriptions. It lists 21 clinical symptoms and physical signs related to the QDBS syndrome. The scale ranges from 0 to 51 with 51 indicating the worst score possible. The higher the score, the more severe the degree of the syndrome. The scale has been developed, validated, and applied in the Department of Neurology, Cardiology, Endocrinology, and multiple investigators have used this method to assess patients with QDBS syndrome. This scale has excellent inter-rater reliability and internal consistency. It is NMPA’s recommended outcome measure in Guideline for clinical research of new Chinese medicine drugs with syndrome.

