### Data Collection and Management

Data will be collected at baseline, at 14, 28, 42, and 56 days post-allocation, and at the 90 days follow-up. To promote data quality, each site’s investigator will be trained centrally regarding the study requirements, including standardized evaluation of scales involved in the trial, operation of the CM tongue and facial imaging and analysis instrument, requirements for serum specimen collection, and on eliciting information from participants in a uniform and reproducible manner.

An electronic data capture system will be used in this study. The investigator/clinical research coordinator (CRC) will input the original data into the electronic data capture system accurately, in a timely, complete, and standard manner. After data entry, data may not be changed at will. If data entries need to be modified, the investigator/CRC will need to record the reason for modification according to the system prompt. All the operations in the system are traceable.

The data manager will develop a detailed data verification plan according to the protocol and case report form, including logic verification, scope verification, time window verification, consistency verification, and compliance verification. The efficiency indicators and key safety indicators should be fully verified to ensure the accuracy and integrity of the data. Data verification should be carried out in the case of an unknown test group, and the generated data query content should avoid deviation or induced questions.

After all the data are inputted and queried, a blind review meeting will be held to determine the data set division. After reaching a consensus on all data questions, the sponsor, principal investigator, data manager, and statistician will jointly sign the approval document for locking the database. After obtaining approval, the data manager will execute the database locking operation and remove the system operation authority of the relevant personnel. The study documents will be retained in a secure location for at least 5  years after trial completion.

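### Missing primary scores are filled by LOCF, and the sensitivity analysis said to hold under missing at random uses LOCF again, so it is mislabelled and cannot test the LOCF assumption

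*Protocol article*

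**What the plan says.** The primary outcome (Primary Outcomes) is "defined as a change in the national approved QDBS syndrome evaluation scale from before to after the 6-week treatment". The Statistical Methods section deals with missing values of that outcome in two consecutive sentences. The first reads "Last observation carry forward (LOCF) approach will be used to impute missing data of primary outcome according to intention-to-treat analysis". The second begins "A sensitivity analysis will be conducted to determine the robustness of the results under the missing at random assumption" and ends by naming its target and its tool: "to evaluate the role of lost to follow-up (i.e., participants who did not follow-up to V4), by using the LOCF method". The article names no other missing-data method.

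Two other statements bear on the point. Statistical Methods also says "Outcome measurements will be analyzed using full analysis sets and per protocol sets according to intention-to-treat (ITT) analysis", so a per protocol result will be reported. Data Collection and Management says "Data will be collected at baseline, at 14, 28, 42, and 56 days post-allocation, and at the 90 days follow-up", but the visible text does not say at which of these visits the QDBS scale is rated, and it does not define V4. Table 1, which may show both, is not reproduced in the text at hand.

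**The concern.** A sensitivity analysis for missing data is useful only if it changes the assumption about the unseen values. Here the main analysis and its check name the same single imputation for the same outcome, and the check is labelled with an assumption that the method does not implement. MAR means that, given the data observed, dropout carries no further information about the missing score, so that score can be predicted from observed scores and their time course. LOCF instead fixes the score at its last value and treats the filled-in number as if it had been measured.

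At stake is the one primary outcome of a phase II trial meant to inform a phase III trial. If LOCF distorts the treatment difference, the planned check would agree with the distorted result.

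**Working it through.** **1. Logic, no figures needed.** Main analysis: week-6 score missing, fill with the last observed score. Sensitivity analysis: week-6 score missing, fill with the last observed score. On the same patients the two completed datasets are identical, and so are the estimates.

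**2. Inputs from the article.** There are 432 patients, three diseases and 1:1 allocation, so 432/6 = 72 per arm per disease. The minimum is stated as "the sample size should not be less than 60 per treatment arm for each disease to estimate the parameter". No dropout rate is given; the implied allowance is 1 - 60/72 = 16.7%.

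**3. Inputs assumed, not in the article.** SD of the change 6; linear improvement over six weeks, equal in both arms when there is no drug effect; dropout 10% in one arm and 23.3% in the other (average 16.7%, gap 13.3 percentage points).

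**4. Bias under no drug effect.** Bias = (gap in dropout) x (mean improvement a dropout misses under LOCF).
- 9-point improvement, last score equally often at baseline, day 14 or day 28: missed (9 + 6 + 3)/3 = 6; bias 0.133 x 6 = 0.80.
- 9-point improvement, last score at day 14 or 28 only: missed (6 + 3)/2 = 4.5; bias 0.60.
- 4-point improvement, day 14 or 28 only: missed (2.67 + 1.33)/2 = 2; bias 0.27.
- 2-point improvement, day 14 or 28 only: missed (1.33 + 0.67)/2 = 1; bias 0.13.
- 9-point improvement, day 14 or 28 only, 14% v 19.3%: 0.053 x 4.5 = 0.24.

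**5. Type I error.** SE = 6 x sqrt(2/n), which is 1.00 at n = 72 and 0.58 at n = 216. Rejection rate = Φ(bias/SE - 1.96) + Φ(-bias/SE - 1.96).

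| Scenario | Bias | 72 per arm | 216 per arm |
|---|---|---|---|
| 9 points, a third carried from baseline | 0.80 | 13% | 28% |
| 9 points, post-baseline only | 0.60 | 9% | 18% |
| 4 points, post-baseline only | 0.27 | 6% | 7% |
| 9 points, 14% v 19.3% | 0.24 | 6% | 7% |
| 2 points, post-baseline only | 0.13 | 5% | 6% |

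Simulations (four visits, within-patient correlation 0.5) agree: about 12-13% and 25-27% in the first row, 9% and 17% in the second, and 5-7% in the rest. The 28% is slightly high because carried-forward values add spread that the formula ignores.

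**6. Equal dropout with a true 3-point effect that grows linearly.** Post-baseline dropout only: 16.7% x 1/2 = 8% lost, leaving 2.75. With a third carried from baseline: 16.7% x 2/3 = 11% lost, leaving about 2.7.

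**7. Direction, and comparison with a MAR method.** A separate large simulation (400,000 per arm) let dropout depend on the last observed score, with a placebo improvement of 6 points, SD 6 and visit correlations 0.7/0.5. Active minus placebo, negative favouring the drug:

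| True effect | Dropout placebo / active | Full data | LOCF | MAR imputation |
|---|---|---|---|---|
| 0 | 16.7% / 16.7% | 0.01 | 0.01 | 0.01 |
| 0 | 10% / 23.3% | 0.00 | 0.58 | 0.00 |
| 0 | 23.3% / 10% | 0.01 | -0.57 | 0.01 |
| -3 | 16.7% / 16.7% | -2.99 | -2.73 | -2.98 |
| -3 | 10% / 23.3% | -3.03 | -2.11 | -3.03 |
| -3 | 23.3% / 10% | -2.99 | -3.43 | -2.99 |

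The MAR method recovers the full-data difference throughout. LOCF does so only with no effect and equal dropout. Running LOCF a second time returns the LOCF column.

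**The case against.** The numbers are chosen, not derived. The article gives no expected improvement, SD or dropout by arm, and a placebo described as indistinguishable from the granules gives no reason to expect dropout to differ twofold. Stable angina and diabetic neuropathy are not described as improving on placebo, and without a time trend unequal dropout alone creates no such bias. Study Design describes three independent populations and Sample Size works per disease, so 72 per arm is the safer basis; the 216 figures apply only if the diseases are pooled. All of this stands, and it is why the size is given as a range.

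A reader might infer that LOCF will manufacture a drug effect, with a false-positive rate near 25%. The documents do not support that. The figure needs a 9-point trend, a 13-point dropout gap, a third of dropouts carried from baseline, and pooling. If active dropout is higher the bias runs against the drug, and equal dropout is conservative.

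The sensitivity sentence is also garbled: it singles out patients not followed to an undefined V4, so a different patient set may have been meant. That would change who is imputed, not the assumption. The per protocol analysis likewise changes the population and leaves the missing-data assumption untouched.

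Finally, one could say that this is phase II and that the full analysis plan may differ. But the article states the rule rather than leaving it open, and its Discussion says that it presents a detailed analysis plan. An unseen plan would have to contradict it.

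**Conclusion.** The point holds as wrong as written. The article assigns LOCF to the primary outcome and again to a check described as holding under MAR. The label does not fit the method, and the check cannot reveal dependence on LOCF. This conclusion needs no assumed figures.

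The consequence is conditional. A time trend together with unequal dropout biases the treatment difference, in a direction set by which arm loses more patients. Equal dropout shrinks an effect that grows over time, by about 8-11% at 16.7% loss. With SD 6 and 10% v 23.3% dropout, bias under no drug effect runs from about 0.3 points (4-point improvement) to 0.6-0.8 points (9-point improvement). Type I error is then about 6-13% at 72 per arm and 7-27% if pooled at 216 per arm. With a small trend or a small imbalance it stays near 5%.

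If the QDBS scale is not rated between baseline and week 6, LOCF becomes baseline carried forward and both faults remain.

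**What to change.** Replace LOCF in the primary analysis with a method valid under MAR. Multiple imputation by arm from baseline and other recorded data works whatever the rating schedule. A mixed model for repeated measures is the alternative if the QDBS scale is rated at the interim visits, which should be confirmed against Table 1.

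Make the sensitivity analysis vary the missing-data assumption, for example by delta-adjusted or reference-based imputation, and define V4. Keep LOCF at most as a supplementary analysis.

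At minimum, rewrite the sensitivity sentence so that it names a MAR-valid method other than LOCF.

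The cost is a little more specification and SAS programming, with no new data. The article says that the plan precedes any analysis and that statisticians are blinded until the trial is completed, so the change can be made before unblinding.
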